1) Recruitment capability and resulting sample characteristics: Recruitment capability will be assessed by the number of individuals expressing interest in study participation, the intervention uptake rate, and the time required to reach the target sample. The traffic light system will evaluate whether the planned sample size (*N* = 60) is achieved within the 12-week recruitment period (see Table 3). Sample characteristics will be collected through sociodemographic data (e.g., age, gender, education, employment, relationship and parental status, residence size, nationality, ethnicity, migration status), family history of anxiety or depression, prior diagnoses, psychotherapy history, current medication or treatment, and experience with digital mental health tools.2) Data collection procedures and outcome measures: The appropriateness of data collection will be assessed through EMA and T2 data completeness, psychometric evaluation of outcome measures, and feedback from the study team. Participant perspectives on acceptability and appropriateness will be gathered at T2 using self-developed items and in the qualitative telephone interviews based on a custom interview guide (IG participants only).3) Acceptability and suitability of intervention and study procedures: Acceptability, satisfaction, and usability of the app will be measured using the German version (ZUF-8; *α* = 0.90, 8 items, score range: 8–32) of the Client Satisfaction Questionnaire (CSQ) (71), the System Usability Scale (SUS; *α* = 0.91, 10 items, score range: 0–40) (72), and self-developed items. At T2, qualitative telephone interviews will further explore participants’ experiences with the app’s features, content, and overall impressions. Intervention adherence will be measured via user engagement metrics (e.g., number of modules and exercises completed, usage days during the 4-week period, buddy interactions, and optional sensor data). Reasons for dropout will be assessed through self-developed items and within the qualitative interview at T2.4) Resources and ability to manage and implement the study and intervention: The study team will document time and personnel resources needed for app development, study administration, and participant support.5) Participant responses to the intervention: Symptoms of anxiety and depression will be measured using the Patient Health Questionnaire Anxiety and Depression Scale (PHQ-ADS; *α* = 0.88–0.92, 16 items; score range: 0–48) (73), which combines the Patient Health Questionnaire 9 (PHQ-9; *α* = 0.89, 9 items, score range: 0–27) (51, 74) and the Generalized Anxiety Disorder Scale 7 (GAD-7; *α* = 0.89, 7 items, score range: 0–21) (75). The PHQ-ADS has shown high internal consistency (*α* = 0.88–0.92). Cognitive behavioral skills will be measured using the Cognitive-behavioral Therapy Skills Questionnaire (CBTSQ; *α* = 0.90, 16 items, score range 16–80), covering behavioral activation (*α* = 0.85) and cognitive restructuring (*α* = 0.88) (76). The Things You Do Questionnaire (TYDQ; *α* = 0.90, 15 items, score range: 0–60) (77) will assess engagement in positive routines and meaningful activities, with higher scores indicating greater engagement (*α* = 0.90). Qualitative interviews at T2 will explore the perceived effects of the app from the IG participants’ perspective.6) Risks and negative events: The benefit–risk ratio will be assessed by tracking adverse events, including reliable symptom improvement and deterioration according to the reliable change index (RCI) by Jacobson and Truax for the PHQ-ADS, indicating a decrease or increase of >1.96 from T1 to T3 as well as suicidal thoughts and behaviors (78). These will be measured at T2 using the INEP-On (Inventory for Assessment of Negative Effects of Psychotherapy adapted to online interventions; *α* = 0.86, 21 items) (79), item 9 of the PHQ-ADS (73), and item 9 from the BDI-II (80). Qualitative interviews will further explore perceived negative effects of the app.

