
**Table 3 tab3:** Traffic light system for assessing feasibility.

Traffic light system for assessing feasibility	Green	Yellow	Red
1. Participants recruited during the planned period (%)	*N* = 60 (100%)	*N* = 45–59 (75–98%)	*N* < 45 (<75%)
2. Participants with complete data at post-assessment (percentage of the total sample)	>70%	50–70%	<50%
3. Completed EMA data (at least one EMA completed per day; percentage of the total sample)	>60%	40–60%	<40%
4. Omega value for two-thirds of the outcome questionnaires	≥0.70	0.60–0.69	<0.59
5. Satisfaction (ZUF-8)	*M* > 26	*M* = 24–26	*M* < 24
6. Pre-post change in the PHQ-4 scores compared to the control group (depression and anxiety subscales)	Baseline score ≤3: No reliable deterioration, indeterminate, or reliable improvement Baseline score > 3: No deterioration or improvement reliable to deterioration and improvement	No improvement reliable to improvement in participants with a baseline score > 3	Symptom deterioration reliable to deterioration
7. Risk–benefit ratio	Positive	Negative: Isolated negative intervention-related events, that can be addressed by revising the intervention or study	Negative: Serious adverse intervention-related events (e.g., suicidal thoughts), symptom deterioration

EMA, Ecological Momentary Assessment; ZUF-8, Questionnaire for Patient Satisfaction 8.

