##### Quantitative data analysis

3.2.5.1

The intervention is considered feasible if all criteria in the traffic light system are rated yellow or green (see Table 3). Yellow ratings will prompt internal discussion and minor adjustments; red ratings indicate the need for major revisions, with input from external experts. Quantitative baseline data will be analyzed descriptively. Mental health outcomes will be examined using analysis of covariance (ANCOVA) to assess between-group pre-post changes, and time series analyses will explore individual symptom trajectories based on 4-day intervals.

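### Table 3, criterion 4: the omega bands leave 0.59 without a colour, and the two-thirds wording does not say whether it is counted within one band or cumulatively

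*Protocol article*

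**What the plan says.** Table 3 (Protocol article, section 3.2.4.2, Feasibility measures) has seven traffic-light criteria. Criterion 4 is headed "Omega value for two-thirds of the outcome questionnaires". Green is 0.70 or more, yellow is 0.60 to 0.69, and red is below 0.59. It belongs to the second feasibility domain, where data collection is judged partly by "psychometric evaluation of outcome measures, and feedback from the study team".

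Section 3.2.5.1 (Quantitative data analysis) gives the table its force: "The intervention is considered feasible if all criteria in the traffic light system are rated yellow or green". For the worst rating it adds that "red ratings indicate the need for major revisions, with input from external experts". It gives no rule for a criterion that ends up with no colour.

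**The concern.** A traffic-light rule has to return exactly one colour for any result. This row falls short in two ways.

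- **The cut-points.** Red stops below 0.59 and yellow starts at 0.60, so 0.59 belongs to neither.
- **The counting rule.** The row speaks of two-thirds of the questionnaires but does not say two-thirds doing what. They could all have to fall inside the same band, or they could have to reach at least the lower limit of a band. The two readings agree when the questionnaires behave alike and can differ when they are mixed.

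At stake is one of the seven rows that together decide feasibility. If the row returns no colour, or a colour that depends on the reading, the rating has to be settled after the omegas are known. That is what a predefined rule is meant to prevent.

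**Working it through.** **Inputs.** The three bands and the two-thirds wording come from Table 3, criterion 4. The all-criteria rule comes from section 3.2.5.1. The number of questionnaires, k, is not given in the article, so k = 3 to 7 is assumed. There is no plan figure to reproduce; the check is whether every possible result receives one colour.

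**Step 1: do the bands meet?**

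| Table 3 row | Green | Yellow | Red | Gap |
|---|---|---|---|---|
| 2, complete post data | >70% | 50–70% | <50% | none |
| 3, EMA completion | >60% | 40–60% | <40% | none |
| 5, ZUF-8 mean | >26 | 24–26 | <24 | none |
| 4, omega | ≥0.70 | 0.60–0.69 | <0.59 | 0.59 |

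Running through 0.00 to 1.00 in steps of 0.01, exactly one value, 0.59, has no colour. With three decimals, 0.590 to 0.599 and 0.691 to 0.699 have none. Rounding to two decimals closes the upper gap (0.691–0.694 become 0.69 and 0.695–0.699 become 0.70). It only shifts the lower one: 0.595–0.599 become 0.60, but everything from 0.585 to 0.594 becomes 0.59.

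The gap can affect the row on either reading. Take three questionnaires: one at 0.70 or above, one at 0.59, one below 0.59. Counted within bands, there is one green, one red and one with no band, so no band holds two. Counted cumulatively, the highest value that two of the three reach is 0.59, which is neither 0.60 nor below 0.59.

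**Step 2: mixed results.** Now set 0.59 aside and class each questionnaire as high (≥0.70), middle (0.60–0.69) or low (<0.59). Let m be the smallest whole number that is at least 2k/3.

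- Number of possible patterns: (k+1)(k+2)/2.
- Patterns in which one given band holds at least m questionnaires: (k−m+1)(k−m+2)/2. Because m is more than half of k, two bands cannot both do so.
- Uncoloured on the within-band reading: (k+1)(k+2)/2 − 3 × (k−m+1)(k−m+2)/2.

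| k | m | Patterns | Coloured (within band) | Uncoloured (within band) | Uncoloured (cumulative) |
|---|---|---|---|---|---|
| 3 | 2 | 10 | 3 × 3 = 9 | 1 | 0 |
| 4 | 3 | 15 | 3 × 3 = 9 | 6 | 0 |
| 5 | 4 | 21 | 3 × 3 = 9 | 12 | 0 |
| 6 | 4 | 28 | 3 × 6 = 18 | 10 | 0 |
| 7 | 5 | 36 | 3 × 6 = 18 | 18 | 0 |

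The cumulative reading is: green if at least m are high; otherwise yellow if at least m are high or middle; otherwise red. It colours every pattern. If half or more are low, at most half reach 0.60, which is fewer than m, so the row is red. The most that can be low without a red is k − m: 1, 1, 1, 2 and 2 for k = 3 to 7.

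**Step 3: consequence for the verdict.** On the within-band reading with k = 6, three high and three low gives no colour. Section 3.2.5.1 requires each criterion to be rated yellow or green. A row without a colour does not meet that, but it does not trigger the red consequence either. Its status is undefined.

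**The case against.** The strongest reply is that this is a one-digit slip plus a sensible shorthand. Most readers would take the two-thirds wording cumulatively, and then no mixed result is unrated. The stated alphas in section 3.2.4.2 run from 0.85 (a CBTSQ subscale) to 0.92 (the upper end for the PHQ-ADS), so omegas near 0.59 look unlikely. Most of this stands, and it limits the size of the point. Two qualifications remain. No alpha is stated for the PHQ-4, and a non-clinical sample with a narrow range of symptoms may show lower reliability than published values. Nor does a plausible reading replace a stated one.

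Three stronger conclusions are tempting, and the document does not support them.

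- A reader might infer that half the questionnaires could be unreliable and the trial still be declared feasible. On the cumulative reading that result is always red. On the within-band reading it has no colour, which is not a pass. With three questionnaires, a result with at least half but fewer than two-thirds low cannot occur at all.
- A reader might infer that scales answered only by the intervention group give omegas too imprecise to use, and that the row should rest on a few baseline scales. The scales about app use (ZUF-8, SUS, INEP-On) have stated alphas of 0.86 to 0.91, and the only four-item scale, the PHQ-4, is not confined to one arm in Table 2. Restricting the set is a design preference, and it would drop the ZUF-8, which alone decides criterion 5.
- A reader might count the missing list of outcome questionnaires as a defect. A journal article commonly leaves such a list to the full protocol or analysis plan.

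**Conclusion.** The gap at 0.59 is an error in the printed rule and depends on no assumption. Criterion 4 is out of line with the percentage and ZUF-8 rows of the same table, whose cut-points meet.

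The two-thirds wording is ambiguous rather than wrong. Whether mixed results go unrated depends on the reading: between 1 of 10 patterns (three questionnaires) and 18 of 36 (seven) within bands, none cumulatively. The counts rest on an assumed number of questionnaires and say nothing about how likely a pattern is.

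The practical effect is small. No false declaration of feasibility follows on either reading, and the stated alphas make an omega in the affected range unlikely. It is a minor correction, worth making because the row is part of the feasibility verdict.

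**What to change.** Replace criterion 4 in Table 3 with an ordered rule, with omega rounded to two decimals:

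- Green: at least two-thirds of the outcome questionnaires have omega of 0.70 or more.
- Yellow: not green, and at least two-thirds have omega of 0.60 or more.
- Red: otherwise. This moves the red cut-point from below 0.59 to below 0.60.

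Every pattern for k = 3 to 7 then has exactly one colour. The cost is one table row, with no new data and no change to the assessments. Compared with the within-band reading, the patterns that had no colour become yellow or red: for six questionnaires the 10 uncoloured patterns split into 6 more yellow (6 to 12) and 4 more red (6 to 10), with green unchanged at 6. The change should be made before any omega is calculated.

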##### Qualitative interviews

3.2.4.3

At T2, qualitative interviews with IG participants will explore experiences related to feasibility criteria (see Table 3), including user satisfaction, usability, and practical applicability in daily life. To ensure data saturation, at least 20 participants will be interviewed (53). Interviews will be conducted by trained staff, audio-recorded, and transcribed verbatim using a standardized guide.

#### Statistical analyses

3.2.5

##### Quantitative data analysis

3.2.5.1

The intervention is considered feasible if all criteria in the traffic light system are rated yellow or green (see Table 3). Yellow ratings will prompt internal discussion and minor adjustments; red ratings indicate the need for major revisions, with input from external experts. Quantitative baseline data will be analyzed descriptively. Mental health outcomes will be examined using analysis of covariance (ANCOVA) to assess between-group pre-post changes, and time series analyses will explore individual symptom trajectories based on 4-day intervals.

##### Qualitative data analysis

3.2.5.2

Qualitative interviews will be analyzed using a qualitative content analysis approach (55), combining inductive and deductive thematic analysis in an iterative process with MAXQDA-24. Transcripts will be coded by two independent raters to ensure inter-coder reliability, following established guidelines (55). The coding guide will be developed through iterative consensus. Based on the findings, an online validation questionnaire will be created and presented to interview participants to assess agreement with the results.

#### Safety concept

3.2.6

Data on adverse and serious adverse events will be collected at different assessment points throughout stage II as recommended (81). Suicidal thoughts and behaviors will be assessed with PHQ-ADS item 9 (73) and BDI-II item 9 (80) at screening, and INEP-On item 20 at T2. Other negative events will be assessed with the INEP-On at T2. Relevant indications may also emerge from participants’ responses during the screening or qualitative post-intervention interview.

A detailed safety protocol, based on existing recommendations (77) outlines procedures for managing negative events. These include automated provision of help resources via questionnaires and email, and individual therapeutic phone consultations following a structured emergency plan tailored to the severity of suicidal ideation. A licensed psychotherapist will be available for consultations, and screening interviewers will be trained and supervised in implementing the emergency plan. All adverse events will be documented.

## Discussion

4

This paper presents the study protocol and concept of one of the first feasibility and acceptability studies of a dyadic, AI-driven JITAI app for the prevention of anxiety and depressive disorders. Developed using a participatory research approach, the CaYou app integrates transdiagnostic CBT components. The study aims at providing early proof-of-concept regarding feasibility, acceptance, and preliminary efficacy of the app. Objective usage data and participant feedback will inform key areas for optimization and guide the design of a future full-scale randomized controlled effectiveness trial.

Despite the innovative approach, the proposed DyAI-JITAI app study also faces several challenges and risks during implementation. (1) A key challenge lies in identifying optimal moments for delivering interventions. The efficacy of the app may be influenced by how accurately the algorithm recognizes patterns and adapts to individual users. This could be more challenging if users have less consistent daily routines during the learning and intervention phases or if their engagement is low, for example due to intervention or assessment fatigue, or a general lack of interest (42). Although JITAIs are designed to adapt to users’ receptivity, reduce intervention fatigue, and support daily-life transfer, these issues may persist. (2) The decision points of the JITAI may not be optimally configured due to limited empirical evidence on the ideal frequency and timing—for instance, how long notifications should remain visible on smartphones, or how many exercises and prompts should be offered and displayed each day (26)—increasing the risk of missing critical intervention windows. (3) Another potential challenge is the buddy’s role in supporting behavior change. While social support can improve engagement, buddies may feel uncertain about how to respond effectively. As the support is intended to be one-sided, perceived asymmetries in responsibility or emotional reciprocity could strain the relationship and reduce the support’s impact. (4) Technical issues or system-generated recommendations that feel irrelevant to users may also lead to frustration and lower motivation for behavior change (42). (5) Recruitment may be difficult due to privacy or ethical concerns regarding active and passive EMA, especially among individuals with subclinical anxiety and depression (83). In addition, the abundance of freely available mental health apps, which are often not evidence-based (84), may reduce the appeal of participating in a study that requires more effort (6). The generalizability of the EMA and geolocation-based approach may be limited by several factors. Users in rural areas may experience challenges with inconsistent cellular coverage and GPS signal quality, affecting location-based triggers and real-time data collection. Additionally, the digital divide may create barriers for populations with limited smartphone access or digital literacy, including older adults and individuals with lower socioeconomic status.

## Conclusion

5

The planned study will offer valuable insights into the real-world feasibility, acceptability, and preliminary clinical relevance of a dyadic, AI-driven JITAI app for the prevention of anxiety and depressive disorders. By integrating structured qualitative data, it will also deepen our understanding of how JITAIs may help close the intention-behavior gap—an essential factor in preventive mental health. The study follows a clear JITAI development framework, enhancing transparency and replicability while generating critical knowledge to guide future evidence-based JITAI designs. By delivering personalized, context-sensitive support in moments of needs, JITAIs can increase the relevance of interventions, thus having the potential to enhance engagement and adherence over time. This mechanism is crucial, as adherence and engagement are closely linked to efficacy and therefore important for behavior change (85). Ultimately, it lays important groundwork for developing effective, scalable interventions that promote sustainable behavior change in everyday life.
